## Abstract

**Background:**

The number of people living with dementia is rapidly increasing. With dementia’s impact on memory, communication, and self-identity, it is important to identify ways of meeting individual needs of diagnosed individuals and their caregivers. This study will test a new intervention, SENSE-GARDEN, that integrates autobiographical music, films, pictures, and scents with innovative technology to create an immersive environment tailored specifically for the individual.

**Objective:**

The SENSE-GARDEN study is an Active Assisted Living Program–funded multicenter project. The primary objective of the study is to assess whether a personalized, innovative technology-based intervention can improve the well-being of older adults living with moderate to severe dementia. The study will also assess whether the intervention can improve coping and reduce burden in caregivers.

**Methods:**

A controlled before-after study design will be used. There will be 3 sites in 3 trial countries: Belgium, Norway, and Portugal. A total of 55 people with dementia (PWDs) will be recruited. All eligible participants for the study will be randomized into the intervention or control group. For the first three months of the study, all participants will receive the SENSE-GARDEN intervention. For the final month of the study, the intervention group will continue visits to the SENSE-GARDEN, and the control group will discontinue visits. A mixed-methods approach will be used, including the use of standardized outcome measures, quantitative physiological data, and qualitative interview data.

**Results:**

The trials commenced recruitment in August 2019, and all data are expected to be collected by the end of May 2020. A user-centered design process is underway, with results from the first phase of user interviews indicating that people with mild cognitive impairment, family caregivers, and professional caregivers consider the SENSE-GARDEN to be a potentially valuable tool in providing numerous benefits to dementia care. Feasibility testing of the SENSE-GARDEN has been completed and results are expected to be published in October 2019.

**Conclusions:**

Findings from the SENSE-GARDEN trials will provide insights into the use of technology for personalizing interventions to the PWD. This will have potential implications on not only dementia research, but it may also have influences on care practice.

**International Registered Report Identifier (IRRID):**

DERR1-10.2196/14096

## Introduction

### Background

Dementia is an umbrella term for a variety of neurodegenerative diseases that most often affect memory, behavior, and communicative abilities [1]. There are approximately 47 million people living with dementia worldwide [2]. With this number set to increase to 131.5 million by 2050, it is of the utmost importance to tackle dementia’s progressive impact on the well-being of people living with a diagnosis. The World Health Organization (WHO) has called for action on dementia, presenting it as a public health priority at a global level [1]. This action includes a call for research to identify ways of supporting the needs of people living with dementia, their caregivers, and society in the context of costs, understanding, and awareness.

People with dementia (PWDs) progressively disconnect from the world; they experience loss of function, especially memory, affecting their cognition, physical activity, and verbal and nonverbal communication. A person’s ability to communicate with others progressively worsens during the course of dementia, which can lead to the individual engaging in problem behaviors as an expression of unmet needs [3,4]. This can then result in an increase in caregiver burden for family members and residential care staff.

Continuing social contact with others and participating in activities is important for maintaining quality of life. Participating in past pleasant activities has an impact on functional ability and psychological well-being for PWDs living in residential care [5]. However, care facilities often struggle to fulfil this need for engagement and active participation, especially for residents in more advanced stages of cognitive and physical impairment [6]. This lack of external stimuli in the care environment can cause PWDs to become increasingly depressed [7].

In recent years, studies have identified numerous complex needs of PWDs living in long-term care. These include management of challenging behaviors, maintenance of social relationships, involvement of people with cognitive deficits in meaningful activities, and supporting the emotional needs of all [8,9]. Emotion-oriented approaches to care have been shown to be cost-effective ways of improving psychological well-being and social behavior among PWDs [10,11]. These nonpharmacological approaches are often person-centered, focusing on the personal, social, and emotional needs of the individual. Reminiscence rooms, virtual gardens, and virtual reality forests are examples of how immersive technologies have been integrated in emotion-oriented approaches designed to create effective interventions for PWDs [12,13]. However, this area of study has called for further research in determining what works best for the individual [6]. It has recently been suggested that an individualized multisensory environment for PWDs would be a highly beneficial intervention, especially if family members are included in the selection of stimuli [14]. Our research builds on this suggestion, creating not only a personalized multisensory intervention but one that also incorporates immersive technology, all with the inclusion of family members, friends, and professional care staff.

### SENSE-GARDEN Intervention

The study is performed as part of the SENSE-GARDEN EU project, funded by the Active Assisted Living (AAL) Program Call 2016. It is a 3-year project that brings together a consortium of partners across Belgium, Norway, Portugal, and Romania. This multidisciplinary project is embracing a user-centered design approach throughout the development and implementation of the intervention. The SENSE-GARDEN intervention addresses the need for individualized approaches to dementia care by creating a multisensory environment that automatically adapts to the individual with dementia. Through integrating autobiographical music, films, images, and scent with technology, the SENSE-GARDEN is able to offer an immersive experience tailored specifically for the individual based on an individual profile including preferences in music, images, videos, and personal media, such as family photos.

The project aims at creating virtual spaces that are automatically adaptable to the personal memories and individual preferences of the users. The design of the space is shown in Figure 1. These spaces will be designed to strengthen the awareness of older PWDs by combining multisensory stimulation with physical activity and techniques from reminiscence therapy and Montessori methods. This stimulation of sight, touch, hearing, balance, and smell is expected to lead to a reconnection with reality for the PWD, resulting in an improvement in overall well-being and quality of life. The intervention will use a combination of various activities and approaches:

*Reality Wall:* This is the projection of landscape videos, with some including familiar scenery and known places, onto a large wall.*Move to Improve:* This is an augmented reality game aimed at improving balance and increasing levels of physical activity.*Memory Lane:* This is an interactive touchscreen device showing family photographs and media from the individual’s life story.*Life Road:* This is a stationary bicycle placed in front of a film showing a familiar place to the PWD.*Sounds Surround Me:* These are sounds from the surrounding sound speakers playing familiar music and background soundscapes.*Scents to Memories:* This is an olfactory dispensary system releasing familiar scents.*Films of My Life:* This is a collection of classic film excerpts meaningful for the PWD, together with family movies.

The rationale to include these elements in the SENSE-GARDEN intervention stems from the current evidence base of ways to improve the well-being of PWDs. For instance, there has been an increasing amount of research on combining biographical information with multimedia apps to create digital *life stories*. Research on multimedia biography apps for PWDs has shown numerous benefits, such as stimulating reminiscence, evoking positive emotions, stimulating social interaction with others, and improving autobiographical memory [15-17].

Research also suggests that there is potential to use technology to create immersive environments in dementia care. A recent study investigated the effects of a *virtual reality forest* on PWDs, in which large screen projection of scenery such as a forest or river was used in combination with movement sensors to create an immersive and interactive environment [13]. Although this environment was not based on the biographical information of the user, results showed improved levels of pleasure and alertness during the intervention.

Considering the promising results of these studies, the innovative approach of SENSE-GARDEN has the potential to provide numerous benefits to its users. Together, it was anticipated that the integration of these components and various stimuli would complement each other to create an immersive environment that the PWD can connect with, for example, pictures of forest scenery could be combined with the sound of singing birds and the odor of a pine forest. Other scenarios may include seas, streets, the beach, urban, or rural areas according to the most meaningful memories of each individual PWD. Having this immersive environment tailored to the individual memories of each user will create a connection to the more active areas of the memory; such stimuli may result in various types of emotional states.

Another important aspect of SENSE-GARDEN is the aim to support PWDs in sharing their life story with a caregiver. The theoretical underpinnings of this aim can be linked to previous study conducted on dementia and narrative. The literature has commented on the important role of digital media in conveying narratives and supporting meaningful conversations for PWDs and their caregivers [18]. By interacting with the various stimuli together with a caregiver, it is hoped that the PWD is able to reminisce on their past and become engaged in the *present moment*. The SENSE-GARDEN encourages PWDs to exercise at both mental and physical levels and takes them back into places they feel connected to. They can, for example, cycle or walk in a well-known space and feel like they are going home. Such experiences may have an effect on invigorating their identity and helping to recover their sense of self.

Relatives will have a key role in the initial adaptation of the space by providing information regarding the past of the user. After this initial setting, the SENSE-GARDEN will automatically adjust to the individual person. Feedback during the sessions will allow the SENSE-GARDEN system to learn the preferences of each user, meaning that the sessions will become increasingly personalized with each visit.

**Figure 1 figure1:**
[figure not shown]
Architectural sketches of the SENSE-GARDEN space (left:interior, right: exterior).

### Objectives

The study will test operational SENSE-GARDENs installed in the 3 study sites: Belgium, Norway, and Portugal. With these countries, a large coverage of the European context is achieved, allowing to study cultural, social, economic, and legal differences between the countries and European regions. The primary objective of this study is to determine whether the delivery of the innovative technology developed in SENSE-GARDEN can improve well-being in older adults with intermediate to advanced dementia. The WHO defines health as the “state of complete physical, mental, and social well-being and not merely the absence of disease or infirmity” [19]. This study will adopt this holistic approach to health and well-being by measuring well-being through primary outcomes related to behavior, activities of daily living, cognitive function, quality of life, self-identity, communication, and social presence.

### Primary Outcomes

The study will examine 2 quantitative and 2 qualitative primary outcomes for the PWD, namely, reduction in behavioral and psychological symptoms in dementia (BPSD), improvement in cognitive function, increase in the feeling of social presence, and an increase in self-awareness and engagement. The primary outcomes for the informal caregiver (family caregivers) are a reduction in carer burden, improvement in carer coping and relief from stress, an increased quality of visits from the informal caregivers to the PWD, and an improvement in the quality of the relationship with their relative with dementia. The primary outcome for the professional caregiver is a reduction in caregiver burnout.

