### Exploratory Outcomes

Some interesting outcomes will be measured with an exploratory aim, but because of their nature as explained ahead, they may not allow for clear conclusions to be drawn. Instead, the purpose of these outcomes is to provide preliminary insights that can be built upon in future studies. These outcomes are as follows: a reduction in depressive symptoms and loneliness, relief from feelings related to the care burden, and improvement in quality of life.

The outcomes regarding depression and relief from feelings related to care burden are measured by means of semistructured interviews. The inclusion of people in later stages of dementia means that there may be challenges in applying these measures to all participants in the study.

A total of 4 months is a short amount of time, and therefore, it is not expected that a large improvement in the quality of life will be observed during this period. However, a small change in the quality of life may provide rationale for future longitudinal studies of the use of SENSE-GARDEN in dementia care, in which quality of life can be examined to a greater extent.

Physiological data will also be collected during the SENSE-GARDEN sessions. The Empatica E4 [20] will be used to collect information on electrodermal activity (EDA) and heart rate. These will be assessed during SENSE-GARDEN visits, as reaction to different stimuli. Data will be collected from a subgroup of participants, depending on their tolerance to use a wristband-mounted device. The device is validated for clinical use. Previous research on nonpharmacological interventions has used the E4 wristband to measure engagement and arousal states in people with mild to moderate dementia [21].

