##### Person With Dementia

###### Primary Outcomes

####### A Reduction in Behavioral and Psychological Symptoms in Dementia

The Bedford Alzheimer Nursing Scale–Severity (BANS-S) [25] and the Cohen–Mansfield Agitation Inventory (CMAI) [26] will be used to determine whether the intervention reduces behavioral and psychological symptoms of dementia. BANS-S is a nursing staff–administered questionnaire that assesses dressing, sleeping, speech, eating, mobility, muscles, and eye contacts in persons with severe dementia. It is a reliable measure with good internal consistency (Cronbach alpha=.64-.80). CMAI is a widely used tool that evaluates aggressive behavior, nonaggressive behavior, and verbally aggressive behavior. The caregiver-rated questionnaire comprises 29 agitated behaviors, each rated on a 7-point scale of frequency ranging from 1 (never) to 7 (several times an hour).

####### Increase in the Feeling of Social Presence

Observational measures will be used to determine the level of social engagement in the participants with dementia. These tools will be the Observed Emotion Rating Scale (OERS) [27], the Verbal and Nonverbal Interaction Scale (VNVIS-CR) [28], and the Observational Measurement of Engagement (OME) [29]. All 3 measures have previously been used in studies observing people living with dementia. OERS assesses pleasure, general alertness, anxiety or fear, and sadness at 10-min intervals. VNVIS-CR is a tool developed specifically to measure verbal and nonverbal interaction in people with mild to moderate dementia. The 26 items assess nonverbal social behaviors, nonverbal unsociable behaviors, verbal sociable behaviors, and verbal nonsociable behaviors. The OME evaluates various dimensions of engagement in people with mild to severe dementia. The tool measures attention to stimulus, attitude toward stimulus, rate of refusal, duration, and activity.

Observations will be made during at least 2 of the SENSE-GARDEN sessions for each participant. For participants in the intervention group, recordings will be taken during a SENSE-GARDEN session in week 4, week 12, and week 16. Participants randomized to the control group will only have recordings taken during a session in week 4 and week 12, as these individuals will no longer be visiting the SENSE-GARDEN after week 12.

####### Improvement in Cognitive Function

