The Mini-Cog [30], the Functional Assessment Staging Tool (FAST) [31], and the Global Deterioration Scale (GDS) [32] will be used to assess whether there is any improvement in cognitive function among the participants. The Mini-Cog is an assessment of cognitive function that only takes 2 to 5 min to complete. It comprises a word recall task and a clock drawing test. FAST is a dementia staging tool that focuses on an individual’s level of functioning and ability to carry out activities of daily living. Scores range from 0 to 7, with a higher score indicating an increased level of functional decline. GDS is a brief dementia staging scale that assesses the stage and progression of dementia in terms of cognitive decline. Scores range from 0 to 7, with a higher score indicating a more severe level of cognitive decline.

####### Increase in Self-Awareness and Engagement

Conversation analysis will be used to assess the PWD’s level of self-awareness and engagement with both the SENSE-GARDEN stimuli and the caregiver conducting the session. To conduct conversation analysis, audio recordings of certain SENSE-GARDEN sessions will be taken.

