### Data Analysis

Quantitative data will be analyzed using SPSS Statistics version 25 (IMB Corp). Stratification by gender, age, and type and stage of dementia will be used to analyze the data. Repeated measures analysis of variance (ANOVA) will be used to assess whether the SENSE-GARDEN intervention has an effect on participants over time. Given the novelty of the SENSE-GARDEN intervention, it is not possible to assess the previous literature for clinically meaningful differences. However, Cohen *d* has been used to determine effect size in studies focusing on the effects of nonpharmacological interventions on behavioral outcomes in PWDs [43].

Cohen *d* is a measure of standardized difference between 2 means [44]. It uses standard deviation units to express the magnitude of difference between the 2 means, indicating the importance of the difference. Cohen has defined a small effect size as *d*=0.2, a medium effect size as *d*=0.5, and a large effect size as *d*=0.8.

For this study, repeated measures ANOVA will be performed on the data using SPSS to assess the effects of the intervention over the numerous time points (T0-T3). We estimate that a sample size of 55 will have over 80% power to detect a medium difference between means at a .05 significance level.

Qualitative interview data will be analyzed using thematic analysis [45]. Thematic analysis is a method of identifying patterns of prevalent ideas or responses and can offer rich insight into the attitudes and beliefs of participants. This aspect of the study will be vital for understanding the users’ experiences of the SENSE-GARDEN.

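### Nine unranked primary outcomes share one .05 and one power figure tied to none of them; the primary list contradicts itself and two scales do not fit their outcome

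*Protocol article*

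**What the plan says.** The Primary Outcomes section of the introduction sets out three groups.

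- **Person with dementia:** "The study will examine 2 quantitative and 2 qualitative primary outcomes for the PWD". In order, these are behavioral and psychological symptoms (BPSD), cognitive function, social presence, and self-awareness and engagement.
- **Informal caregiver:** "The primary outcomes for the informal caregiver (family caregivers) are a reduction in carer burden", followed by coping and stress, quality of visits, and quality of the relationship.
- **Professional caregiver:** "The primary outcome for the professional caregiver is a reduction in caregiver burnout".

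Objectives describes the primary set differently: "measuring well-being through primary outcomes related to behavior, activities of daily living, cognitive function, quality of life, self-identity, communication, and social presence". Exploratory Outcomes ends its own list with "relief from feelings related to the care burden, and improvement in quality of life", and the later description of QUALID under Outcome Measures is again filed as exploratory.

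Table 1 assigns the scales. The Outcome Measures text says that BANS-S, used for BPSD, "assesses dressing, sleeping, speech, eating, mobility, muscles, and eye contacts in persons with severe dementia", and that FAST, used for cognitive function, looks at "level of functioning and ability to carry out activities of daily living".

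Data Analysis plans a repeated measures ANOVA over T0-T3. It claims over 80% power with 55 participants for a medium difference "at a .05 significance level". No outcome is named for that statement, and no other significance level appears in the article.

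**The concern.** A trial with one significance level needs to say which result that level governs. Here nine outcomes have equal standing, most have a scale of their own or several, and the power sentence does not say which one it is about. The article therefore does not settle what would count as the trial's main finding, and the .05 cannot be read as the error rate of the overall conclusion.

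Three inconsistencies make this worse, because even the set of primary outcomes is unclear. Quality of life is both primary and exploratory. Social presence seems to be labelled qualitative but is rated numerically. Two scales can make a primary outcome look improved although their own descriptions are mostly about something else.

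**Working it through.** **1. The plan's own power figure.** Inputs from Data Analysis: N = 55, medium effect d = 0.5, level .05 (taken as two-sided), four time points. The correlation between time points is not given, so it is varied.

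- Paired t, one within-person test: noncentrality 0.5 × √55 = 3.71, power 95%. If d is on the raw SD, the standardized change is 0.5/√(2(1−ρ)), and power is 73% at ρ = 0, 87% at 0.3 and 95% at 0.5.
- Repeated measures ANOVA, time effect: f = 0.25, λ = f² × 55 × 4/(1−ρ) = 13.75/(1−ρ), df 3 and 162, sphericity assumed. Power is 88% at ρ = 0, 97% at 0.3 and 99.6% at 0.5.

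So over 80% is reproduced for **one** within-person test on **one** scale with 55 people. It cannot cover burnout, which rests on 3 × 3 = 9 professional caregivers (Participants section): paired power at d = 0.5 is about 26%.

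**2. Counting outcomes and scales** (Primary Outcomes; Table 1).

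| Outcome | Measure | Scales |
|---|---|---|
| BPSD | CMAI, BANS-S | 2 |
| Cognitive function | Mini-Cog, FAST, GDS | 3 |
| Social presence | OERS, OME, VNVIS-CR | 3 |
| Self-awareness and engagement | conversation analysis | 0 |
| Four informal-caregiver outcomes | ZBI, Brief-COPE, FAVS-D, QCPR | 4 |
| Burnout | MBI-HSS | 1 |

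Outcomes: 4 + 4 + 1 = 9. Scales: 2 + 3 + 3 + 0 + 4 + 1 = 13, serving eight outcomes. The three social-presence scales are scored only during sessions. They have no T0 value (Table 1) and no week-16 value in the control group (Outcome Measures), so they do not fit a T0-T3 ANOVA. That leaves 13 − 3 = 10.

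**3. Chance of at least one false positive if each scale total were tested at .05.** For independent tests it is 1 − 0.95^k. For correlated tests, two-sided z statistics with a common pairwise correlation were simulated (200,000 replicates). The correlations are assumptions.

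| Scales | Independent | ρ = 0.3 | ρ = 0.5 | ρ = 0.7 |
|---|---|---|---|---|
| 10 | 40% | 35% | 29% | 21% |
| 13 | 49% | 42% | 33% | 24% |

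If the 13 scales correlate only within each population (blocks of 8, 4 and 1), the figures are 45% at 0.3 and 40% at 0.5.

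**4. Cost of correcting across all scales.** Bonferroni over 13 gives .05/13 = .0038. The paired-test power in step 1 then falls from 95% to 75%. One named outcome keeps 95% at a 5% error rate.

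**5. Places that conflict.**

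- *Quality of life and activities of daily living:* Objectives has both among the primary outcomes. Primary Outcomes has neither. Both exploratory sections hold quality of life, and the introduction expects no large change in it within four months.
- *Social presence:* two of the four outcomes are called quantitative and two qualitative. Read in list order, social presence is qualitative, yet it has three rating scales.
- *BANS-S:* serves BPSD, but the described content is mainly function and physical severity.
- *FAST:* serves cognitive function, but is described as functional staging.

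**The case against.** **No testing rule is stated.** A reader might infer that all the scales are each tested at .05 and that any one of them would be claimed as success. The article does not say so. Its only .05 is in the power sentence, conversation analysis has no test attached, and a multiplicity rule may sit in an analysis plan that is not shown. This stands, which is why the error rates above are conditional. It does not answer the rest: the article itself fixes which outcomes are primary, it does so inconsistently, and an unseen plan would not reconcile its sections.

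**A false positive is not likely in the sense of more than even odds.** That stronger reading is tempting, but 49% is the ceiling for 13 scale totals, and it needs independence.

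**Three populations may be three families.** This is a fair position, since caregiver burden and coping are separate aims. It reduces the problem without removing it: the five scales for the person with dementia that fit the ANOVA give 1 − 0.95^5 = 23%, and the four caregiver scales give 1 − 0.95^4 = 19%.

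**Low power between arms is a different issue.** A two-sample comparison of 27 and 28 at d = 0.5 has about 44% power even at .05. A reader might blame multiplicity for that. However, Data Analysis speaks of an effect over time, and the within-person test keeps most of its power after adjustment, so the low between-arm figure should not be used to enlarge this point.

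**The quality-of-life conflict is one loose sentence**, and only two of 13 scales are mismatched. Both are true. These are wording repairs, and they add no tests. The article also acknowledges its small sample and limited generalizability, but it still sets a primary objective of showing improved well-being.

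**Conclusion.** The point holds in this form: nine unranked primary outcomes, eight of them on 13 rating scales, with one level and one power statement attached to none. If the scales were each tested at .05, the chance of at least one false positive would be about 40% (10 scales) to 49% (13 scales) under independence and about 29-42% at correlations of 0.5-0.3, against a nominal 5%. This rests on one test per scale total and on assumed correlations; stronger correlation would lower it.

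The status of quality of life and activities of daily living is contradictory as written. The classification of social presence is unclear, since it depends on reading the list in order. BANS-S and FAST do not match their outcomes on the article's own descriptions; the mismatch does not extend to the scales in general. The documents do not establish that every scale will be tested at .05 or that a chance success is more probable than not.

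**What to change.** - Name one lead primary outcome and one scale for the person with dementia, and tie the .05 and the power statement to it. CMAI is a reasonable candidate, but it is described as covering agitated behavior only and the documents do not compel it; the sponsor may choose another.
- Report the remaining scales as secondary with effect sizes and confidence intervals, or apply Holm, within each population if preferred.
- Remove quality of life and activities of daily living from the primary list in Objectives, so that it agrees with Primary Outcomes and both exploratory sections.
- State whether social presence is a quantitative outcome. If it is, say how it is analyzed without a T0 value and without week-16 values in the control group.
- Move BANS-S and FAST to functional secondary outcomes beside WHODAS 2.0.

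The cost is relabelling and some analysis wording. Fewer outcomes can be called primary. Data collection does not change.
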